### Data Analysis

#### End Points

The uptake, acceptability, and feasibility of using PrEP will be examined by the end points documented in Textbox 3.

End points of the Be-PrEP-ared study.Preventive needs:Recruitment rate (number of screened participants/number of registered on study-specific website)(Un)safe sex behavior during the last 6 monthsPercentage of reported intention to use pre-exposure prophylaxis (PrEP) in the future at final visitRetention rates in the different regimensAttitudes towards PrEP use: satisfaction and motivation for future useAdherence:(In)consistent pill take, percentage of days with no pill taken/days on which a pill should have been takenTenofovir drug levels in blood and/or hair samplesPerceived skills to adhere, including self-efficacyImpact of PrEP use on other preventive strategies:Number of sex partnersSelf-reported condom useSex under influence (alcohol, drugs)Impact of PrEP use on sexually transmitted infection (STI) trends (descriptive analyses only):STI incidence and trends: *Chlamydia trachomatis* / *Neisseria gonorrhoeae*, *Mycoplasma genitalium* / *Trichomonas vaginalis*, herpes simplex virus-2, syphilis, and hepatitis CSafety of the different regimens of PrEP use:Rate of adverse events related to PrEPReal-life effectiveness of PrEP use:Incidence of HIV infection by regimenGenotypic viral resistanceFeasibility of oral fluid self-sampling testing:Feasibility

A mixed method analysis of quantitative and qualitative end points will be conducted by triangulating the results from both data collection types.

#### Clinical Data Analysis

The study design is observational, and all analyses will be descriptive. As participants may change regimens, a single participant may be included in different regimens over time and contribute to person-months of daily, event-driven, or no use in the analyses.

Adherence may be dichotomized as adherent/nonadherent and is defined in general as the proportion of pills the participant needed to take that were actually taken. The number of pills actually taken is calculated based on self-reporting through the diary. Different indicators for adherence will be used for each of the regimens and per 3 months:

Adherence to regimen: number of pills taken/number of pills which should have been taken according to the PrEP dosing regimen.Estimated proportion of covered sex acts: number of sex acts covered with PrEP/number of sex acts. This indicator will be calculated separately for high-risk sexual activities and low-risk sexual activities. High-risk sexual activities are defined as anal intercourse without a condom with a partner of unknown HIV status or known to be HIV positive with detectable virus load.

Exploratory analysis of predictors of retention on PrEP or (non)adherence may be performed using regression models (linear, logistic, or Cox-regression). Different groups may be considered for analysis depending on the change of regimen: group remaining on daily use, group remaining on event-driven, group changing from daily to event-driven, and group changing from event-driven to daily use.

All nonserious and serious AEs will be grouped according to a prespecified side-effect coding system and tabulated. The number of subjects experiencing any AE, any SAE, and any drug-related SAE will be summarized by PrEP regimen.

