### Participants

Eligibility is assessed using the inclusion and exclusion criteria as shown in Textbox 2.

Selection criteria of the Be-PrEP-ared study.Inclusion criteria:Able and willing to provide written informed consentBorn to male sex (including transgender females)Aged 18 years or moreHad sex with a man in the last 12 monthsHIV negative (confirmed at enrollment)Reporting at least 1 criterion for high risk:- Condomless anal intercourse in the last 6 months with a casual partner with unknown HIV status or HIV positive status- A sexually transmitted infection episode in the last 6 months- Having taken post-exposure prophylaxis in the last 6 monthsAble and willing to participate in the project as required by the protocol for 18 monthsMotivated to strengthen prevention efforts, including willingness in starting to use pre-exposure prophylaxisExclusion criteria:Having symptoms or clinical signs consistent with acute HIV infectionBeing allergic to the active substances or any of the excipientsHaving an estimated creatinine clearance of <60 mL/minute/1.73 m² according to the CKD-Epi formula (Chronic Kidney Disease Epidemiology Collaboration)Having an active hepatitis B infectionTaking HIV post-exposure prophylaxisParticipating in other clinical studies (phase I-III) or another research project related to HIV and antiretroviral therapy

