### Sample Size

Given the provided funding, we included 200 MSM at high risk of acquiring HIV. The sample size was determined to estimate the proportion of participants who are nonadherent. Using the normal approximation for the calculation of the 95% confidence interval and using the worst-case value for proportion of nonadherence of 0.5 with 200 participants, the proportion of nonadherence can be estimated to a precision of 7%.

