### Online Diary

The participant is asked to complete an online diary with information regarding pill intake, number of rectal and oral sex acts, and an individual risk assessment of acquiring HIV for each day participated in the study. A Web platform is created where participants can log in with a personal account using their smartphone, laptop, or other devices. They are instructed to complete the online diary every day or at least twice a week to limit recall bias. At every visit, and more clearly emphasized at the month 1 visit, the social scientist or designee examines all diaries for completion to allow for optimal data collection and verifies whether participants encountered problems or difficulties or unclear procedures when completing the online diary. Participants also receive an email when they have not completed their diary for more than 7 days. Event-driven users are able to complete the diary only during sexual active periods. In addition, a paper version is available if preferred. Finally, an audit trail is available.

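### The high-risk act definition leaves out condomless anal sex with an HIV-positive partner of unknown viral load, so PrEP coverage of high-risk acts may be misstated

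*Protocol article*

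**What the plan says.** The protocol article's Clinical Data Analysis section gives two adherence indicators, each by regimen and per 3 months. The second is "Estimated proportion of covered sex acts: number of sex acts covered with PrEP/number of sex acts". The section adds: "This indicator will be calculated separately for high-risk sexual activities and low-risk sexual activities". High-risk activities are then defined as "anal intercourse without a condom with a partner of unknown HIV status or known to be HIV positive with detectable virus load". Low-risk activities get no definition.

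The Participants section (Textbox 2) uses a related phrase for eligibility. One of three alternative risk criteria is "Condomless anal intercourse in the last 6 months with a casual partner with unknown HIV status or HIV positive status", with no condition on viral load.

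The Online Diary section describes daily recording of "information regarding pill intake, number of rectal and oral sex acts, and an individual risk assessment of acquiring HIV". It does not name condom use, partner HIV status or partner viral load, although the article may have shortened the list.

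**The concern.** The split has two named classes but one definition, and the definition treats missing knowledge in opposite ways. Not knowing a partner's HIV status makes an act high-risk. Knowing that he has HIV, but not his viral load, takes the act out of high-risk. The second act is at least as strong a candidate for the high-risk class as the first.

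Adherence to the two regimens is a primary objective, and this indicator is the one of the two in Clinical Data Analysis that ties pill use to exposure. If exposed acts are left out of the high-risk class, the coverage reported for that class describes only some of the acts a reader would expect it to describe. The same omission would recur in every regimen and every 3-month table.

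**Working it through.** **1. The plan's own figure.** The Sample Size section gives a precision of 7% with 200 participants and a proportion of 0.5. Check: 1.96 × √(0.5 × 0.5 / 200) = 0.0693, or 7%. It reproduces. It concerns the proportion nonadherent and does not depend on the act split.

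**2. The rule applied to each kind of partner (condomless anal act).**

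| Partner | First limb: HIV status unknown | Second limb: HIV positive and detectable | Class as written |
|---|---|---|---|
| HIV status unknown | met | – | high-risk |
| HIV positive, known detectable | not met | met | high-risk |
| HIV positive, viral load unknown | not met | not met | not high-risk; otherwise unstated |
| HIV positive, known undetectable | not met | not met | not high-risk |

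The third row is the gap. If low-risk is the complement of high-risk, these acts are low-risk. If not, they appear in neither class, and the two denominators no longer add up to the total number of acts. No literal reading makes them high-risk.

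**3. Effect on high-risk coverage.** Let u be the share of all risky acts (rows 1 to 3) that fall in row 3, c_h the coverage of rows 1 and 2, and c_u the coverage of row 3.

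- As written: c_h
- With row 3 included: (1 − u) × c_h + u × c_u
- Change: u × (c_u − c_h)

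The documents give no act counts, partner mix or coverage rates. All values below are assumptions chosen to show a range.

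| u | c_h | c_u | As written | Row 3 included | Change (points) |
|---|---|---|---|---|---|
| any | 90% | 90% | 90.0% | 90.0% | 0 |
| 1% | 90% | 50% | 90.0% | 89.6% | −0.4 |
| 5% | 90% | 50% | 90.0% | 88.0% | −2.0 |
| 10% | 90% | 50% | 90.0% | 86.0% | −4.0 |
| 20% | 90% | 50% | 90.0% | 82.0% | −8.0 |
| 10% | 80% | 95% | 80.0% | 81.5% | +1.5 |
| 20% | 80% | 95% | 80.0% | 83.0% | +3.0 |

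**4. Effect on low-risk coverage, if low-risk is the complement.** Assume 400 risky acts, u = 10% (40 acts) and 600 other acts covered at 70%.

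- c_u = 50%: as written (0.70 × 600 + 0.50 × 40) / 640 = 440 / 640 = 68.8%, against 70.0% without the 40 acts.
- c_u = 95%: as written (420 + 38) / 640 = 71.6%, against 70.0%.

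**5. The entry criterion beside the analysis definition.** The entry criterion applies to persons ("Reporting at least 1 criterion for high risk"), looks back 6 months, is limited to casual partners and is one of three alternatives. The analysis definition applies to single acts during follow-up, adds a viral-load condition and drops the restriction to casual partners. The same act can thus qualify a man for entry and later not count as high-risk.

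**The case against.** The strongest case against is that this is coding detail. The source is a journal article. How a residual class or a 'do not know' answer is handled is normally settled in the full protocol, analysis plan or codebook, none of which is shown. That would answer a complaint about missing detail. It does not fully answer this one, because the article states the high-risk rule, and the stated rule excludes these acts.

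Three stronger readings are tempting, and the documents support none of them.

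- **The plan assigns these acts to low-risk.** It does not say so. Low-risk is undefined, and treating it as the complement is an inference.
- **The definition contradicts the entry criterion.** An eligibility screen for persons and a classification of acts serve different purposes and may differ. Men who enter through a recent STI or post-exposure prophylaxis need not have reported any such act. The difference is an unexplained mismatch.
- **Coverage of risky acts is misreported.** This cannot be shown. If row 3 acts are covered as well as the others, nothing changes. If men take more care with a partner they know has HIV, the shift is upward.

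It is also fair to say that the reach is small. Textbox 3 does not list covered acts among the adherence end points. Pill adherence to regimen, overall act coverage and drug levels are untouched. The section states that "The study design is observational, and all analyses will be descriptive", so no test or error rate rests on the split.

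**Conclusion.** The point stands in a limited form. As written, the high-risk definition omits condomless anal acts with an HIV-positive partner of unknown viral load, while it includes acts with a partner whose HIV status is unknown. The omission follows from the wording alone and needs no assumption.

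The consequence does need assumptions. Reported high-risk coverage may be off by u × (c_u − c_h). Over the values tried, including these acts changes it by between −8 and +3 percentage points, with zero possible. The documents fix neither size nor direction. The effect is confined to one descriptive stratification of one adherence indicator, and no figure stated in the article changes. It is worth correcting because the correction is simple.

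**What to change.** Redefine high-risk activities as condomless anal intercourse with a partner whose HIV status is unknown, or with an HIV-positive partner who is not known to have an undetectable viral load. Define low-risk activities as all other acts, so that the two denominators sum to the total.

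Check that the source used to classify acts records condom use, partner HIV status and partner viral load, with 'viral load unknown' as a possible answer. If that answer is missing, it can be added only for the remaining follow-up. For acts already recorded, an HIV-positive partner without a recorded undetectable viral load would fall in high-risk under the new wording.

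Add a sentence explaining why the act definition uses viral load when the entry criterion does not. A further tabulation counting every HIV-positive partner as high-risk is optional.

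Cost: one sentence of definition, one recode and possibly one answer option. The high-risk denominator grows, and reported coverage may change slightly in either direction.

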#### Questionnaire Data Analysis

Analysis of the questionnaire data will be mainly descriptive, using uni- and bivariate statistical analyses. Depending on the results, multivariable statistical models and longitudinal analyses may be used. All computations will be done using SPSS version 23.0 (IBM Corp).

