The slow recruitment rate was mainly due to limited staff resources (ie, limited availability of study physicians) resulting in approximately 4 screenings per week. This could be an important limitation, as those enrolled first could differ from those enrolled last (ie, as PrEP use is at least 1 year apart) and thus would not be comparable. Media coverage or PrEP availability, changing sexual norms within the community, and related factors may have had a different influence on participants. However, the study may reflect actual willingness to use PrEP and allows for exploring how an evolving HIV prevention landscape including access to PrEP affects individual PrEP uptake and adherence. Moreover, it cannot be excluded that individual differences between the start and end of the study will be the result of similar influences rather than PrEP use on its own.

Conducting a demonstration project such as Be-PrEP-ared may in itself have an impact on HIV prevention that goes beyond providing ARV medication to participants. It has reinforced collaborations with community organizations and health care providers and can help in increasing PrEP awareness and influence policy on HIV prevention. In the wake of Be-PrEP-ared, various substudies have already started in Belgium such as a survey among health care providers to assess their PrEP knowledge, attitudes, and willingness to prescribe. New studies are being set up in this evolving field, which will be important to allow for crossnational research. To develop a good understanding of how to optimally implement and provide PrEP integrated into the existing health care structures, new research will be of paramount importance.

In conclusion, results from this study will contribute to a better understanding of PrEP users’ experiences including their choices for specific PrEP regimens. The findings will help to inform appropriate delivery strategies for the roll-out of PrEP and for policy makers to consider financial reimbursement of PrEP in Belgium.

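### Grouping men by whether they later change regimen would, if used to compare retention, make switching look protective when it has no effect

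*Protocol article*

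**What the plan says.** All statements are in the protocol article.

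- Clinical Data Analysis sets the general approach: "The study design is observational, and all analyses will be descriptive". It handles regimen changes by time-updating: "a single participant may be included in different regimens over time and contribute to person-months of daily, event-driven, or no use in the analyses".
- The same section then adds an optional layer: "Exploratory analysis of predictors of retention on PrEP or (non)adherence may be performed using regression models (linear, logistic, or Cox-regression"). The next sentence says that groups may be considered according to change of regimen, namely "group remaining on daily use, group remaining on event-driven, group changing from daily to event-driven, and group changing from event-driven to daily use".
- Adherence indicators are to be calculated for each regimen and for each 3-month period.
- Investigational Product lets every participant switch, discontinue or restart at each follow-up visit. Study Visits and Table 1 give 18 months of follow-up. Truvada is supplied at six follow-up visits (months 1, 3, 6, 9, 12 and 15).
- End Points (Textbox 3) lists retention in the different regimens, and adherence, among the end points for the primary objectives.

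**The concern.** The four groups are defined by what happens after day 0. A man who stops at month 3 without having switched cannot become a changer unless he returns to PrEP. A man who switches at month 12 must have been using PrEP at that visit. Counted from day 0, the changers' time before the switch is event-free by construction, which is immortal time. A retention comparison between such groups favours changers whatever switching really does.

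The groups also fit poorly with the rest of the section. The person-month approach recognises a state of no use. The four groups do not, although retention is one of the two outcomes named for the regressions. A man who stops is either left in his last group or dropped from all four, and the text does not say which. In the first case the comparison is biased. In the second the outcome has been removed by the grouping.

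For adherence measured period by period, the fault is conditioning on a future switch rather than immortal time in the strict sense. A second question arises there: up to six 3-month records come from the same man, and the text does not say whether a regression would use one summary per man or all the records.

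The Discussion expects insight into factors influencing PrEP use and regimen choice, with implications for policy. A false finding that switchers stay on PrEP longer would feed that advice.

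**Working it through.** **1. The plan's own figure.** Sample Size gives N = 200, worst-case proportion 0.5, 95% interval, normal approximation. Half-width = 1.96 × √(0.5 × 0.5 / 200) = 0.0693, which rounds to the stated 7%. It assumes one record per man and does not involve the four groups.

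**2. Null model for retention.** The article gives no stopping or switching rates, so these are assumptions: per-visit stopping p = 3-8% and switching s = 5-15%. There are six visits, switching has no effect on stopping, nobody restarts, and men who stop are counted in the group they were in when they stopped.

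Base case p = 0.05, s = 0.06, with stopping applied before switching at each visit:

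- q = (1 − p)(1 − s) = 0.95 × 0.94 = 0.893
- Never switched, still on PrEP: q⁶ = 0.5071
- Never switched, stopped: p(1 − q⁶)/(1 − q) = 0.05 × 0.4929/0.107 = 0.2303
- All stopped: 1 − 0.95⁶ = 0.2649, so switched and stopped: 0.2649 − 0.2303 = 0.0346
- Switched, still on PrEP: 0.7351 − 0.5071 = 0.2280
- Stopping among remaining: 0.2303/0.7374 = 31%; among changing: 0.0346/0.2626 = 13%
- Odds ratio: (0.2303/0.5071)/(0.0346/0.2280) = 3.0, where the truth is 1

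If switching is applied before stopping, never-switched stoppers are 0.94 × 0.2303 = 0.2165 and switched stoppers are 0.2649 − 0.2165 = 0.0484. The odds ratio becomes (0.2165/0.5071)/(0.0484/0.2280) = 2.0.

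The same formulas at the corners of the assumed range give these odds ratios:

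| p, s | Stop first | Switch first |
|---|---|---|
| 3%, 5% | 2.8 | 1.9 |
| 3%, 15% | 3.9 | 2.4 |
| 8%, 5% | 3.0 | 2.0 |
| 8%, 15% | 4.2 | 2.6 |

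The range is about 1.9 to 4.2; simulation over the same rates reached 4.3.

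**3. The same data, time-updated.** In the base case, person-visits at risk before any switch are (1 − q⁶)/(1 − q) = 0.4929/0.107 = 4.607. All person-visits at risk are 0.2649/0.05 = 5.298, leaving 0.691 after a switch. Stopping per visit is 0.2303/4.607 = 0.05 before and 0.0346/0.691 = 0.05 after. The ratio is 1 and the bias is gone.

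**4. Continuous-time check.** Assumptions: constant and equal stopping hazards before and after switching, switching only at months 1, 3, 6, 9, 12 and 15, 18-month stopping 10-40% and switching 20-40%. Fixed groups (changed versus stayed) gave a rate ratio of 0.43-0.48 and a Cox hazard ratio of about 0.39-0.52, against a true value of 1. Time-updated person-months gave 0.98-1.02.

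**5. Repeated adherence records, if pooled as independent.** With m = 6 periods per man and an assumed within-man correlation ρ, the design effect for a person-level predictor is 1 + (m − 1)ρ. The true standard error exceeds the naive one by its square root:

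- ρ = 0.3: √2.5 = 1.58
- ρ = 0.5: √3.5 = 1.87
- ρ = 0.7: √4.5 = 2.12

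Nominal 95% intervals would then cover about 78%, 71% and 64%.

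**The case against.** The strongest reply is that the article commits to none of this. Both sentences say may, the regressions are labelled exploratory, and the section calls all analyses descriptive. It does not say that the four groups are covariates in a Cox model or that changers are counted from day 0. They could be descriptive strata, which would be harmless. The section also opens with time-updated person-months that include no use, which is most of the remedy. All of this stands, and it is why the point is conditional. It does not remove the point: the groups are offered for analysis immediately after the retention and adherence regressions, and nothing restricts them to description.

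The size can also be challenged. It rests on assumed rates and on an arbitrary order of events within a visit, which alone moves the base case from 3.0 to 2.0. It also requires men who stop to be kept in a group. The direction is firm under that reading; the magnitude is a range only.

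Three stronger readings are tempting and not supported:

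- That repeated records will be analysed as independent. The text names only "regression models (linear, logistic, or Cox-regression"). One summary per man, robust errors or mixed versions of these models would all fit, and an article commonly leaves such detail to the full plan. Time to first discontinuation has one event time per man in any case.
- That longitudinal methods for adherence depend on the results. The sentence "Depending on the results, multivariable statistical models and longitudinal analyses may be used" concerns questionnaire data, whereas the number of pills taken comes from the diary.
- That the authors treat calendar drift as unresolvable. The Discussion only leaves this possibility open: "individual differences between the start and end of the study will be the result of similar influences rather than PrEP use on its own". That is an honest statement of a limitation.

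**Conclusion.** The concern holds in conditional form. If the four change-of-regimen groups are used to compare retention from day 0, switching would appear to protect against stopping with no true effect. The spurious odds ratio is about 1.9 to 4.2 for assumed stopping of 3-8% and switching of 5-15% per visit, equivalent in the continuous-time check to a hazard ratio of roughly 0.4-0.5 in favour of switchers. If men who stop are instead left out of all four groups, the groups cannot describe retention at all.

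The clustering point is secondary and also conditional. Only if 3-month records are modelled as independent would standard errors be too small, by a factor of 1.6-2.1 for an assumed within-man correlation of 0.3-0.7.

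A reader might infer that the plan as written produces biased results or undermines the study's main estimate. The article does not support that: the analyses concerned are optional and exploratory, and the descriptive estimate of nonadherence and its 7% precision are untouched. The change is still worth making, because retention and adherence are end points for the primary objectives and the remedy extends an approach the section already contains.

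**What to change.** - **Retention.** Build one record per participant and interval. Use regimen at the start of the interval (daily, event-driven, none) as a time-updated covariate, with discontinuation and switching as outcomes, in a Cox model with start-stop records. Alternatively use a landmark analysis: classify men still on PrEP at a fixed visit by their regimen history to that point, and count discontinuation only afterwards.
- **Four groups.** Keep them for description only, and state where men who stop or restart are counted.
- **Adherence.** State whether the model uses one summary per man or the 3-month records. If the latter, use GEE, a mixed model or cluster-robust standard errors.

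The cost is a few sentences of analysis text and modest programming. Regimen changes, discontinuations and 3-month adherence are already collected. The downside is wider intervals for the exploratory results.

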### Investigational Product

Truvada is used for PrEP in this trial. One daily film-coated tablet contains 200 mg of emtricitabine and 245 mg of tenofovir disoproxil fumarate.

When eligible, participants can self-select between 2 different PrEP dosing regimens:

A pill every 24 hours (further referred to as daily)Starting dose before anticipated sex and 1 pill daily during a sexual active episode (further referred to as event-driven). This is the regimen which has been described by the Ipergay protocol (Figure 1) [4]:

A dose of 2 pills between 2 and 24 hours before having sex (or 1 pill if the most recent dose was taken between 1 and 6 days ago)A tablet of Truvada every 24 hours (starting when the first 2 tablets are taken) during the period of sexual activity including after the last sexual intercourseFinally, a last dose of 1 tablet of Truvada approximately 24 hours laterTablets need to be taken every 24 hours with a window period of 2 hours before or after the scheduled time.

All participants, irrespective of their regimen, can opt to switch regimen and to discontinue or to (re)start using PrEP at every FU visit at the HIV/STI clinic at ITM. Before being given a new supply, the participant must be confirmed to be HIV negative using HIV point-of-care tests.

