### Safety

Safety and tolerability of Truvada is evaluated by recording adverse events (AEs) and grading laboratory and vital signs evaluations in the electronic case report form (eCRF) starting from enrollment until the final visit. Severity, causality, and outcome are also assessed by the study physician. Any event that occurred before the enrollment visit is documented as medical history. All AEs are followed up until resolution to the extent possible. An HIV infection is not considered a serious adverse event (SAE). Due to the possible renal adverse effects of Truvada, elevations in serum creatinine are monitored closely. Truvada will be interrupted when creatinine clearance is below 60 mL/minute/1.73 m² and will be permanently discontinued when the clearance stays below 50 mL/minute/1.73 m² after repeat testing.

All SAEs whether or not deemed drug-related or expected are reported within 24 hours (1 working day) to the sponsor (ITM). Line listings of all reported SAEs are sent to the concerned ethics committee (EC) and the Belgian Competent Authority (CA) on a yearly basis. In addition, all fatal or life-threatening suspected unexpected serious adverse reactions (SUSARs) need to be reported to the Belgian CA and to the concerned EC within 7 days. Nonfatal and non–life-threatening SUSARs must be reported within 15 days. Gilead Sciences is notified immediately in case of SUSARs and will receive SAE listings every 2 weeks.

No formal data safety monitoring board (DSMB) has been set up due the fact that this drug is widely used and approved for treatment and prevention of HIV infection by the FDA and EMA. However, an independent data safety monitor has been appointed to review all SAE reports. In case of major safety concerns, this monitor may advise the sponsor to halt recruitment of the trial and/or organize a formal DSMB with a complete overview of the available safety data.

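### The by-regimen adverse event summary does not match the safety endpoint: relatedness is applied only to serious events, and the unit is a subject count not tied to the person-months planned elsewhere

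*Protocol article*

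**What the plan says.** **Endpoint.** In Textbox 3 (End Points), the heading on safety of the different regimens carries a single item, the rate of AEs related to PrEP. The item itself does not say by regimen; that comes from its heading and from the secondary objective in Textbox 1 on the safety of daily and event-driven use.

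**Analysis.** Clinical Data Analysis has two sentences on AEs. One is general: "All nonserious and serious AEs will be grouped according to a prespecified side-effect coding system and tabulated". The other gives the by-regimen summary: "The number of subjects experiencing any AE, any SAE, and any drug-related SAE will be summarized by PrEP regimen".

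**Exposure.** The same section opens with a rule for its analyses as a whole: "a single participant may be included in different regimens over time and contribute to person-months of daily, event-driven, or no use in the analyses".

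**Switching.** Under Investigational Product, all participants "can opt to switch regimen and to discontinue or to (re)start using PrEP at every FU visit".

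**Causality.** Under Safety: "Severity, causality, and outcome are also assessed by the study physician".

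**The concern.** The endpoint and the summary meant to report it differ in two ways.

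1. **Which events.** The endpoint covers all AEs related to PrEP. In the by-regimen summary the any-AE row ignores cause, and the only row that uses cause is limited to serious events. Nonserious related events are counted inside any AE and are never separated out. The general tabulation covers all AEs but mentions neither relatedness nor regimen.
2. **Which unit.** The endpoint is a rate and the summary is a number of subjects. When one person can contribute to several regimens for different lengths of time, that number rises with time on the regimen even if the underlying hazard is the same.

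An analyst who followed the AE sentence literally would not report the stated safety endpoint. A reader comparing daily with event-driven use could take a difference in exposure for a difference in safety.

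**Working it through.** **The plan's own figure.** The only statistical figure in the article is the 7% precision for nonadherence, obtained "using the worst-case value for proportion of nonadherence of 0.5 with 200 participants". It reproduces: 1.96 × √(0.5 × 0.5 / 200) = 0.0693. It has no bearing on AEs, for which the article states no rate or precision.

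**Endpoint against planned outputs**

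| | Relatedness | Seriousness | By regimen | Unit |
|---|---|---|---|---|
| Endpoint (Textbox 3) | related | all | yes, from its heading | rate |
| Row: any AE | any cause | all | yes | subjects |
| Row: any SAE | any cause | serious | yes | subjects |
| Row: drug-related SAE | related | serious only | yes | subjects |
| General AE tabulation | not mentioned | all | not mentioned | not stated |

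No row agrees with the endpoint on both relatedness and seriousness.

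**Effect of exposure on subject counts.** Inputs from the article: 200 participants, 18 months of follow-up (at most 200 × 18 = 3,600 person-months), and a possible regimen change at every follow-up visit. Assumptions, because the article gives no AE rates or switching frequencies: a constant hazard λ, equal in both regimens, and the exposure times t shown. The chance of being counted at least once is P = 1 − exp(−λt).

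*Different spells on a regimen, λ per person-year*

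| λ | 18 months | 6 months | 3 months | Ratio 18 to 3 |
|---|---|---|---|---|
| 0.3 | 36.2% | – | 7.2% | 5.0 |
| 0.5 | 52.8% | 22.1% | 11.8% | 4.5 |
| 1.0 | 77.7% | – | 22.1% | 3.5 |

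At λ = 0.5 the 18- to 6-month ratio is 52.8 / 22.1 = 2.4.

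*One participant's 18 months split between two regimens, λ per person-month*

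| λ | 15 / 3 months | 12 / 6 months | 9 / 9 months |
|---|---|---|---|
| 0.01 | 13.9% / 3.0% | 11.3% / 5.8% | 8.6% / 8.6% |
| 0.02 | 25.9% / 5.8% | 21.3% / 11.3% | 16.5% / 16.5% |
| 0.05 | 52.8% / 13.9% | 45.1% / 25.9% | 36.2% / 36.2% |

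The 15/3 split gives ratios of about 4 to 5, the 12/6 split just under 2, and the 9/9 split exactly 1. The expected number of events per person-month is λ in both regimens in every cell.

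*An assumed whole cohort.* Suppose 150 stay on daily use, 20 stay on event-driven use and 30 move from daily to event-driven at month 6, with λ = 0.02 per month.

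- Daily: 150(1 − e^−0.36) + 30(1 − e^−0.12) = 48.7 subjects of 180 (27.1%), over 150 × 18 + 30 × 6 = 2,880 person-months.
- Event-driven: 20(1 − e^−0.36) + 30(1 − e^−0.24) = 12.4 subjects of 50 (24.9%), over 20 × 18 + 30 × 12 = 720 person-months.

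The raw counts differ 3.9-fold (48.7 / 12.4), close to the 4-fold ratio of person-months. The percentages of subjects differ little. The distortion therefore depends on how exposure is distributed and on whether counts or percentages are read, and in a cohort with few switchers it can be small for percentages.

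**The case against.** The strongest reply is that exposure time is already in the plan. The section's opening sentence assigns person-months of daily, event-driven and no use to the analyses in general, and the AE sentences stand in that section. All AEs are tabulated and causality is assessed. Row lists, denominators and interval methods usually belong in the full protocol or SAP, which are not shown. The word rate is also loose in Textbox 3, where the recruitment rate is a simple ratio of screened to registered. Finally, the analyses are descriptive, regimens are self-selected, no between-regimen safety test is planned, and the illustrated ratios rest on assumed hazards and splits.

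Much of this stands. A reader might infer that the plan ignores exposure time and cannot deliver its safety endpoint. The documents do not support that: person-months by regimen are planned, and the rate can be computed from data the trial says it gathers. A reader might also infer that nonserious AEs go unreported, or that one regimen will look safer. The first is contradicted by the general tabulation, and the second cannot be judged without the exposure figures.

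The mismatch remains. The article did not leave the by-regimen summary open; it named the rows and the unit, and neither fits the endpoint. Even if rate is read as a proportion of subjects, the row for all related AEs by regimen is still not named. The general person-month rule does not say how an AE is assigned to a regimen, and the AE sentence names a number of subjects.

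**Conclusion.** The point holds as a mismatch between endpoint and analysis, of moderate weight because safety is a secondary objective analysed descriptively. The relatedness part rests on the text alone and needs no assumption. The exposure part is conditional: if the subject counts are reported without the planned person-months, they partly measure time on each regimen. The size in this trial is unknown. With equal hazards in both regimens it is about 2- to 5-fold in the chance of being counted, for assumed hazards of 0.3 to 1.0 per person-year or 0.01 to 0.05 per person-month and unequal exposure, and nil when exposure is equal.

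**What to change.** In Clinical Data Analysis, align the AE summary with Textbox 3:

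- Add PrEP-related AEs, serious and nonserious, by the regimen in use at onset (daily, event-driven, no use), and state that assignment rule.
- Report events, and subjects with at least one event, per 100 of the person-months already planned. For the subject-based rate, stop person-time at the first event on that regimen. Dividing subjects by total person-months would still vary with exposure: at 0.05 per month, 52.8% / 15 = 3.5 against 13.9% / 3 = 4.6 per 100 person-months.
- Give 95% confidence intervals that allow for repeated events in the same participant.
- Keep the three subject counts already listed as supplementary rows, with person-months beside them.

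The cost is a few lines of text and a small amount of programming. Causality is already assessed. The article does not state that AE onset dates and regimen start and stop dates are recorded, so confirm that they are in the case report form.
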